#### Safety Criteria and Reporting

AEs will be reported according to the Common Terminology Criteria for Adverse Events (version 5.0). All AEs will be reported up to 4 weeks after the study procedure. Serious AEs will be reported to the ethics committee. Serious AEs that are related to the surgical procedure, without a likely relation to the study intervention, are reported through yearly line listing to the ethics committee. These events are bladder perforation, bladder infection, and hematuria requiring bladder catheterization.

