### Study Procedures

#### Standard Procedure

The standard procedure is the TURBT. After regional or general anesthesia, a resectoscope is inserted into the bladder through the urethra. First, endoscopic inspection of the bladder wall is performed to identify tumors and suspicious lesions. Then, the identified tumors are resected using a loop wire with electric current. After resection of the tumor and retrieval of the resected tissue, the resection bed and edges are cauterized to ensure hemostasis. Subsequently, the resectoscope is removed, and, in most cases, a catheter will be inserted. Resected tissue is sent to pathology to determine the definitive stage and grade. Figure 1 provides an overview of the standard procedure and the schedule of the interventions.

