#### OCT Measurements

During the standard TURBT procedure, the OCT measurements will be performed. After the inspection of the bladder and before the resection of the identified bladder tumors, the OCT catheter will be inserted through the working channel of the rigid resectoscope. The tumors will then be imaged with the OCT catheter tip at approximately 1 cm from the tumor. Approximately 5 measurements will be performed for each suspected lesion and tumor and 3 for a selected region of normal bladder wall. When the OCT measurements are finished, the OCT catheter is removed from the bladder, and the urologist will continue with the standard procedure. The resection of the tumors is performed according to standard care. However, the pathology specimens of each separate tumor will be collected and numbered according to the tumor numbers used during the OCT measurements and sent to the pathologist. After completion of the resection, the OCT catheter will be reinserted through the working channel of the rigid resectoscope, and approximately 3 OCT measurements will be performed on each resection bed. After these measurements, the OCT catheter will be removed from the bladder, and the urologist will continue with the standard procedure (Figure 1).

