### Study Timeline

Patients will be identified at the outpatient clinic, and patients meeting the inclusion and exclusion criteria who provide informed consent will be scheduled for TURBT within 6 weeks of identification. The TURBT and the OCT catheter procedure will be performed as described previously. The procedural timeline of the TURBT is illustrated in Figure 1. After undergoing TURBT, participants will continue with standard treatment. Serious adverse events (AEs) will be monitored and recorded for a period of 4 weeks. Study participation will conclude at the end of this monitoring period.

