## Discussion

### Anticipated Findings

The anticipated principal finding of this study is that the novel MEMS-based forward-looking OCT catheter is safe to use and feasible for generating in vivo cross-sectional images of the bladder wall and tumor during TURBT, with most images suitable for interpretation. This IDEAL phase 2a study represents a critical step in evaluating cystoscopic OCT as a potential imaging tool to aid bladder cancer diagnosis and staging.

The principal findings of this feasibility study will provide critical insights into the utility of the new OCT system in visualizing bladder wall architecture and tumor invasion and grading. Furthermore, this study will provide insights into the clinical and technical obstacles that new devices face when being integrated into the diagnostic process of bladder cancer. In comparison with the current gold standard—histopathological evaluation following TURBT—OCT may enable more immediate, noninvasive diagnostic support, potentially streamlining treatment decision-making. Previously, 3 other forward-looking OCT probes have been studied on bladder tissue and showed that OCT is able to distinguish different layers of the bladder and, in most studies, was able to distinguish malignant tumors from benign tumors [16-21,26,27]. However, the previously studied OCT systems available for bladder wall imaging had, among other constraints, a limited field of view and a low frames-per-second rate, limiting their ease of use and the quality of the OCT images [16,21,27]. In contrast, our system has incorporated technical improvements, such as an improved OCT system with an operating wavelength centered at 1060 nm—which is optimal for imaging in water and forward-looking MEMS-based scanning mirror technology—that altogether enhance image acquisition, resolution, and usability. Importantly, this study will also explore secondary outcomes such as measurement duration and the ability to image resection beds.

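### The yearly line listing for three surgery-related serious AEs, read literally, also takes events possibly related to the new OCT catheter

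*Protocol article*

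**What the plan says.** The protocol article, Safety Criteria and Reporting, begins with a default: "Serious AEs will be reported to the ethics committee". It gives no time limit for that route. An exception follows: "Serious AEs that are related to the surgical procedure, without a likely relation to the study intervention, are reported through yearly line listing". The next sentence closes the list: "These events are bladder perforation, bladder infection, and hematuria requiring bladder catheterization".

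Three other places bear on the point:

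- **How the catheter is used.** Under Standard Procedure, "a resectoscope is inserted into the bladder through the urethra". Under OCT Measurements, before resection "the OCT catheter will be inserted through the working channel of the rigid resectoscope", and later "After completion of the resection, the OCT catheter will be reinserted through the working channel of the rigid resectoscope". Imaging is done from about 1 cm.
- **What is expected of the device.** Sample Size and Enrollment says that this catheter has had no human feasibility study in bladder cancer. Anticipated Findings says: "The anticipated principal finding of this study is that the novel MEMS-based forward-looking OCT catheter is safe to use".
- **Other oversight.** Study Timeline says: "Serious adverse events (AEs) will be monitored and recorded for a period of 4 weeks". Data Monitoring describes independent monitors. Ethics Approval and Amendments provides for a yearly progress summary to the committee, which includes serious AEs.

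**The concern.** Causality judgements usually have a middle ground between unlikely and likely. The article's rule puts that middle ground on the slow side: whatever is not *likely* device-related, and is related to the surgery, goes to the listing.

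The middle ground is realistic for these three events. Resection can cause each of them, and an instrument passed into the bladder twice in the same session could contribute. Imaging at a distance lowers the chance of direct injury during measurement but does not cover insertion and reinsertion.

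What is at stake is the ethics committee's chance to act on a possible device signal while patients are still being treated with a catheter that has no earlier human feasibility study in this disease.

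**Working it through.** The plan gives no figure to reproduce. The check has three parts: where each event goes, when the listing falls due, and how many patients are treated by then.

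**1. Routing under the text as written.** The article has no causality scale, so the words *unlikely* and *possible* below are mine.

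| Event | Relation to OCT | Route |
|---|---|---|
| One of the three, surgery-related | unrelated or unlikely | yearly listing |
| One of the three, surgery-related | possible | yearly listing (literal reading) |
| One of the three, surgery-related | likely or stronger | default route |
| One of the three, not surgery-related | any | default route |
| Any other serious AE | any | default route |

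Only the second row is in question.

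**2. Timing.** Inputs: approval on November 7, 2024 (Ethics Approval and Amendments) and projected end in November 2025 (Results). Inclusion cannot start before approval, so this is the longest span up to the projected end.

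- November 7, 2024 to November 7, 2025: 365 days.
- To November 1, 2025: 365 − 6 = 359 days.
- To November 30, 2025: 365 + 23 = 388 days.

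The article does not say when the yearly cycle starts, so I tried three assumptions:

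- *From approval:* the first listing is due on day 365, within the projected end month. The next is due on day 730, after the study.
- *From first inclusion:* the first listing is due on day 365 or later, possibly after the end.
- *By calendar year:* a listing falls on December 31, 2024, day 23 + 31 = 54. The next falls on day 54 + 365 = 419, after day 388.

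Under each assumption at most one listing falls within the study. Under the first two it falls at or near the end. Under the third, any event after day 54 is listed only after the projected end.

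**3. Progress by then.** Results reports 16 enrolled and 13 completed as of November 2025.

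- Of those enrolled: 13/16 = 81%.
- Of the 15 feasible procedures at which inclusion stops: 13/15 = 87%, if all 13 count as feasible.
- Of the maximum of 25: 13/25 = 52%.

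More than half are treated on every denominator.

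**4. Is there a faster route elsewhere?** The progress summary is also yearly. Investigators and monitors may know of an event sooner, but the article does not say that they then tell the committee.

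**The case against.** The strongest reply is that this rests on one word in a condensed article. Causality categories and reporting deadlines normally sit in the full protocol, which is not shown, and their absence here is no fault. The phrase may be meant only to separate events due to the surgery from events due to the study intervention, with *unlikely or unrelated* intended. Periodic listing of known resection complications is also a sensible choice, since every patient has the resection anyway.

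Much of this stands. The operative rule may already be right, and the listing itself should stay. But the article does not leave the threshold out; it states one, and absence of a likely relation is not the same as an unlikely relation.

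A reader might also infer three stronger things that the documents do not support:

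- *That safety evidence is lost, or that a conclusion on safety is undermined.* AEs are collected for 4 weeks whichever route applies, and monitors verify the data against source documents. Only the date on which the committee hears of certain events changes.
- *That the number of affected events, or the chance of at least one, can be estimated.* The article gives no rate of possibly device-related events, and an assumed range would be too wide to inform severity.
- *That reports would be late by a known amount.* The default route has no stated time limit, so there is nothing to measure the delay against.

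**Conclusion.** The point holds as a minor fault in a stated rule. Read literally, the threshold sends the three surgery-related serious AEs to a yearly listing even when a relation to the new catheter is possible. In a study of about one year (359 to 388 days from approval to projected end) at most one listing falls due, so the ethics committee could be told only after most procedures are done. The sample size, endpoints, analysis and safety data set are untouched.

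The conclusion rests on the literal reading of the article, on the projected end being kept, and on the three assumed starts of the listing cycle. No date of first inclusion is given. With 13 procedures completed against a stop at 15, the study may overrun, and a further listing might then fall within it. Few participants may remain to benefit, but the article plans larger studies that could inherit the wording.

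**What to change.** In Safety Criteria and Reporting, limit the yearly line listing to the three named serious AEs when they are related to the surgery **and** a relation to the OCT catheter or its insertion is judged unrelated or unlikely. Send any of the three with a possible, uncertain or stronger relation to the ethics committee by the ordinary serious AE route. If the full protocol already sets this threshold, no change of procedure is needed; only the article's sentence should be corrected to match.

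The cost is one sentence and a few more individual reports, some of which will turn out to be ordinary TURBT complications. Clearly surgical events stay in the listing, so the exception keeps its purpose. No extra patients, procedures or pause in inclusion are needed.

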### Ethical Considerations

#### Informed Consent

Patients will be informed about the study by their treating physician at the outpatient clinic. If interested, a second appointment will be planned with one of the investigators. All patients will be fully informed about the aims of this study, possible AEs, and the investigational procedure. Written informed consent is obtained from all participants before enrollment (refer to Multimedia Appendix 1 for the informed consent form). All physicians who may potentially see an eligible patient at the outpatient clinic are informed about the study procedures and criteria to ensure identification of potential participants.

#### Ethics Approval and Amendments

This study was approved on November 7, 2024, by the institutional review board of the Amsterdam UMC. All substantial amendments will be notified to the medical ethics review committee; nonsubstantial amendments will be recorded and filed by the sponsor. A summary of the trial progress will be submitted to the medical ethics review committee yearly, including information on the date of inclusion of the first participant, the number of participants included, the number of participants who have completed the trial, and serious AEs.

#### Provisions and Compensation

Provisions for ancillary and posttrial care are not applicable to this study design. The sponsor has insurance coverage for participants that provides compensation for injury or death directly attributable to the study.

## Results

As of November 2025, 16 participants have been enrolled, and 13 have already successfully completed the study procedure. The projected end date of this study is November 2025, and results are expected to be published in March 2026.

## Discussion

### Anticipated Findings

The anticipated principal finding of this study is that the novel MEMS-based forward-looking OCT catheter is safe to use and feasible for generating in vivo cross-sectional images of the bladder wall and tumor during TURBT, with most images suitable for interpretation. This IDEAL phase 2a study represents a critical step in evaluating cystoscopic OCT as a potential imaging tool to aid bladder cancer diagnosis and staging.

The principal findings of this feasibility study will provide critical insights into the utility of the new OCT system in visualizing bladder wall architecture and tumor invasion and grading. Furthermore, this study will provide insights into the clinical and technical obstacles that new devices face when being integrated into the diagnostic process of bladder cancer. In comparison with the current gold standard—histopathological evaluation following TURBT—OCT may enable more immediate, noninvasive diagnostic support, potentially streamlining treatment decision-making. Previously, 3 other forward-looking OCT probes have been studied on bladder tissue and showed that OCT is able to distinguish different layers of the bladder and, in most studies, was able to distinguish malignant tumors from benign tumors [16-21,26,27]. However, the previously studied OCT systems available for bladder wall imaging had, among other constraints, a limited field of view and a low frames-per-second rate, limiting their ease of use and the quality of the OCT images [16,21,27]. In contrast, our system has incorporated technical improvements, such as an improved OCT system with an operating wavelength centered at 1060 nm—which is optimal for imaging in water and forward-looking MEMS-based scanning mirror technology—that altogether enhance image acquisition, resolution, and usability. Importantly, this study will also explore secondary outcomes such as measurement duration and the ability to image resection beds.

One strength of the study lies in its integration into the routine clinical workflow without introducing significant treatment delays. However, this study also has important limitations. Most notably, no histopathological samples are taken from areas of the bladder deemed “normal.” This choice is deliberate and ethically justified; obtaining such biopsies would require additional surgical interventions that are not part of standard care and would therefore introduce unnecessary risks such as bladder perforation or bleeding. Instead, the assessment of the normal bladder wall will be based on the judgment of an experienced urologist during cystoscopy. Another limitation is the single-center design, which may limit the generalizability of the results because outcomes could be influenced by the urologist’s level of experience. However, this limitation is acceptable for an IDEAL phase 2a feasibility study.

Within the IDEAL framework, future studies will aim to validate these findings in larger, multicenter cohorts, with structured training modules for OCT image interpretation, and incorporate learning curves in the study outcomes. Further development may include the integration of artificial intelligence–based image analysis to support real-time diagnosis. In future research, correlation of OCT findings with clinical outcomes such as recurrence or progression could also enhance its clinical relevance. Nevertheless, for integration into clinical practice, the cost-effectiveness of OCT compared to TURBT remains an aspect that should be further studied.

The findings from this study will be published in open-access peer-reviewed journals and will be presented at urology and imaging conferences. In addition, results will be shared with clinical and research communities through institutional networks and multidisciplinary meetings, enabling translation into larger-scale clinical trials and potential clinical implementation if further validated.

### Conclusions

This trial aims to demonstrate the feasibility of using a newly designed MEMS-based OCT catheter and OCT system for the acquisition of diagnostic OCT images in human bladders. If the hypothesis is validated, it will lay the groundwork for a larger, multicenter trial to assess the diagnostic accuracy of OCT in staging and grading bladder cancer. The ultimate goal is to evaluate the potential role of this new OCT catheter and system as a real-time, noninvasive adjunct to standard cystoscopic assessment.

## Appendix

Multimedia Appendix 1 Informed consent form.

## Abbreviations

AE: adverse event
IDEAL: idea, development, exploration, assessment, and long-term study
MEMS: microelectromechanical systems
OCT: optical coherence tomography
AE: adverse event
TURBT: transurethral resection of the bladder tumor
UMC: University Medical Center
WHO: World Health Organization
WLC: white light cystoscopy
